## Abstract

**Background:**

Although China has a large number of older people living with diabetes and hypertension, the primary care system is underdeveloped and so management of these conditions in community care settings is suboptimal. Studies have shown that the collaborative care model across care settings that address both pharmacology and nonpharmacology interventions can achieve hypertension control for older people with diabetes. Barriers to implementing and evaluating this model of care are widely recognized in low and middle-income countries including China.

This study will therefore test the hypothesis that a hypertension management program built on collaboration between hospitals and community health service centers in China can improve blood pressure control in people aged 60 years and older with diabetes as compared to usual care.

**Methods:**

A cluster randomized controlled trial will randomly allocate 10 wards from four hospitals in Nanchang to either an intervention group (*N* = 5) or a usual care group (*N* = 5). At least 27 participants will be recruited from each ward and the estimated sample size will be 135 patients in each group. The intervention includes individualized self-care education prior to discharge and 6-month follow-up in community health service centers. Health professionals from both hospitals and community health service centers will be resourced to collaborate on the implementation of the postdischarge interventions that reinforce self-care. The primary outcome is systolic blood pressure at 6-month follow-up adjusted for baseline value. Secondary outcomes are self-care knowledge, treatment adherence, HbA1c and lipid levels, quality of life, the incidence of adverse events and the incidence of unplanned hospital readmission at 6-month follow-up adjusted for baseline value. A multilevel mixed-effect linear regression model will be used to compare the changes in health outcomes between the intervention and usual care groups.

**Discussion:**

This study will determine whether collaborative care among health professionals between hospitals and community health service centers will improve hypertension management for older people with diabetes in the study sites. The program, if effective, will have an immediate application to hypertension management in the healthcare system in China.

**Trial registration:**

Australia New Zealand Clinical Trials Registry, ACTRN12617001352392. Retrospectively registered on 26 September 2017.

**Electronic supplementary material:**

The online version of this article (10.1186/s13063-018-2766-5) contains supplementary material, which is available to authorized users.

## Background

It is estimated that one third of adults (over 100 million) with type 2 diabetes around the world live in China [1]. One third of the Chinese population are expected to be aged 60 years and older (430 million people) by the year 2050 [2]. The continuous growth of the older population will inevitably increase the incidence of hypertension and diabetes in this population group, resulting in an increased burden on the healthcare system. Hypertension frequently coexists with diabetes. It is reported that 50–80% of patients with diabetes are affected by concurrent hypertension [3]. People with comorbidity of diabetes and hypertension are associated with two times higher risk of developing cardiovascular disease and 7.2 times higher mortality rate compared to those who have diabetes only [4, 5]. Clinical studies have indicated that cardiovascular events and hypertension-related mortality in patients with diabetes can be significantly reduced by optimal hypertension management [6, 7]. However, in China only 14.9% of patients with coexisting hypertension and diabetes have their blood pressure controlled and the disease burden on the health systems is widely reported [8]. Although a primary care approach to hypertension management is well recognized as the most cost-effective way to reduce the disease burden [9], there are no practice guidelines for hypertension management at the community level in China and evidence on how to support the development of this care approach is lacking. This study will add research evidence to the international community to inform practice by exploring a postdischarge intervention to improve hypertension management for older people with diabetes codelivered by health professionals working in hospital and primary care settings in Nanchang, China.

Factors associated with uncontrolled hypertension among older people with diabetes include patient factors (i.e., the lack of knowledge, skill and resources to perform self-care) and healthcare system factors (i.e., the lack of continuity of care and collaboration between different care providers) [2, 10, 11]. Poor communication and collaboration between hospitals and community health service centers exists in many low and middle-income countries which leads to fragmented healthcare delivery for discharged patients [12–14]. Although community health service centers have been established in China to strengthen primary care, collaboration between these centers and hospitals is underdeveloped. A study on healthcare referral services in four cities of China, including Nanchang, revealed that 57% of GPs never had communication with specialists [15]. A population-based study showed that only 34% of residents considered the use of community health service centers in Changsha, China [16]. The main factors contributing to the underutilization of primary care appear to be the lack of effective mechanisms to enable referrals to GPs from hospital specialists, and the lack of communication and collaboration between hospital care and primary care providers [12, 15].

In this study context, after hospital discharge, patients who are not managed by GPs and community nurses usually seek treatments in hospitals only when their conditions get worse [13]. As limited time is available for each patient, the treatment at hospitals mainly focuses on medication, but without attention to nonpharmacological interventions, such as health education to improve patients’ self-care capabilities. This acute and episodic treatment is not in line with contemporary self-care principles that encourage patients to actively engage in their chronic condition management through goal-setting and regular review [17]. Improvements in referral to and capacity-building of the primary care system will enable patients to use primary care as the main source of care to improve both pharmacological and nonpharmacological interventions.

A body of evidence shows that up to 50% of community-dwelling older people in the USA had one or more geriatric conditions such as incontinence, falls, malnutrition, cognitive impairment and pressure ulcers [18, 19]. These conditions compound the complexity of hypertension and diabetes, and contribute to adverse outcomes and hospital admission [20]. Community-dwelling older people who are susceptible to or have these geriatric conditions require primary care services to achieve a long-term control of these conditions, rather than relying on irregular outpatient clinic visits or admission to hospital.

Studies have demonstrated that close collaboration between hospitals and community health service centers can provide patients with continuous and integrated care delivery, which is recognized as an effective approach to improve quality of care, decrease healthcare utilization and reduce costs associated with hypertension treatment [12, 21, 22]. Randomized controlled trials in high-income countries with well-developed healthcare systems and health insurance schemes have demonstrated that multifactorial interventions delivered by a multidisciplinary team involving nurses and doctors had positive effects in hypertension management for older people with diabetes [23–25]. This management often incorporates the following components: health education at hospital and community healthcare settings, healthy lifestyles (i.e., weight loss, smoking cessation, salt and alcohol restriction, increased physical activity), medication adherence and intensification, timely medication adjustment and complication prevention, and continuous and rigorous follow-up visits in primary care [23, 26–29]. Reports of intervention programs including a combination of these components remain scarce in the low and middle-income countries with lower health resources in primary care such as China.

In this study, collaboration between hospitals and community health service centers will be developed to promote a primary care approach to managing hypertension for older people with type 2 diabetes. This collaboration will support the capacity-building of the primary care system in chronic disease management. We hypothesize that a hypertension management program built on collaborative care among health professionals within and between hospitals and community health service centers will improve blood pressure control among community-dwelling older people with diabetes in Nanchang, China.

## Methods

### Study design

A cluster randomized controlled trial will commence at hospitals via discharge and then continue at community health service centers for 6 months in Nanchang, the capital city of Jiangxi Province in China. This cluster design will minimize the risk of contamination between intervention and usual care groups and reflect the classification of public hospitals in China at three levels, namely community health service centers, secondary hospitals and tertiary hospitals [30]. Tertiary hospitals are the final referral hospitals and provide more comprehensive care services for patients compared with secondary hospitals. The Standard Protocol Items: Recommendations for Interventional Trials (SPIRIT) that provide an overview of the schedule of enrolment, interventions and assessments are presented in Fig. 1. The SPIRIT checklist is shown in Additional file 1. The timeline diagram is presented in Fig. 2.

**Fig. 1 Fig1:**
[figure not shown]
SPIRIT figure. GP general practitioner, HbA1 glycosylated hemoglobin

**Fig. 2 Fig2:**
[figure not shown]
Timeline diagram

### Ethical approval and consent to participate

The study protocol was approved by the Southern Adelaide Clinical Human Research Ethics Committee in Australia (Approval Number: 345.16) and the Department of Scientific Research Management at the Health and Family Planning Commission of Jiangxi Province, China. All participants and health professionals delivering the interventions will be given written information so that they can provide informed consent. Each participant and participating health facility will be given a unique numerical code to ensure anonymity. Information provided by participants will be collected in a de-identifiable form and treated confidentially. Data collected through this study will be stored in a secure area in the University that the first author is enrolled in a PhD program. All study-related data will only be accessible to the researchers.

### Eligibility: inclusion criteria and exclusion criteria

Hospitals are eligible for recruitment if they have cardiovascular wards and geriatric wards that predominantly provide care services for older people with hypertension. Participants from these wards are eligible for recruitment if: (1) they receive care for both type 2 diabetes and hypertension from one of the four hospitals selected for the study; (2) the reason for hospitalization is uncontrolled hypertension and/or associated complications; (3) they are diagnosed with coexisting type 2 diabetes and hypertension; (4) they are aged ≥ 60 years; (5) they are fit for discharge justified by the specialist; (6) they are without cognitive impairment (assessed by the Mini-Mental State Examination); and (7) they reside in residential areas where the six community health service centers provide care services.

Participants will be excluded if they are: (1) diagnosed with type 1 diabetes; (2) unable to participate in the study because of severe organ damage, disability, cognitive impairment and other life-threatening disease; (3) unwilling to return to a community health service center for follow-up visits; and (4) living outside of these six communities.

### Randomization

Participants will be recruited from hospitals and continue the trial at community health service centers. Randomization will be performed based on the ward clusters rather than participants. Health professionals involved in the study practice are in a single ward only, therefore the chance of contamination between intervention and usual care wards in the same hospital is very low. There are six secondary hospitals and five tertiary hospitals that provide in-patient care for patients with diabetes and hypertension in Nanchang. As part of the ethics application processes, researchers in the project sent out invitations to all of these 11 public hospitals in Nanchang and informed them that two secondary hospitals and two tertiary hospitals would be randomly selected. The number of hospitals to be included in the trial was estimated on the sample size calculation. In total, six secondary hospitals and five tertiary hospitals agreed to participate. To ensure the selected hospitals are representative of the hospitals in Nanchang, two hospitals will be randomly selected from each level. There are two eligible wards in each participating secondary hospitals and three eligible wards in each tertiary hospital. To ensure the selected wards are representative of the wards in each level of the selected hospitals, three wards from tertiary hospitals and two wards from secondary hospitals will be randomly assigned to either an intervention group or a usual care group. The group assignment will be undertaken by a PhD fellow who is not involved in the trial and is blind to the wards. Patients who meet the inclusion criteria in these participating wards will be invited to the trial. There are six community health service centers that provide chronic disease management for residents in Nanchang. The invitations were sent to these community centers and all of them agreed to participate in the trial. A flow chart of the randomization is shown in Fig. 3.

**Fig. 3 Fig3:**
[figure not shown]
Flow chart of the randomization

### Description of the interventions

The interventions were developed from a comprehensive literature review about effective hypertension management for older people with diabetes. The intervention will start from the hospital with individualized discharge education provided by the patient’s in-charge nurse and the medical specialist (first stage of intervention). After patients are discharged, and in addition to the usual follow-up in the hospital outpatient clinic, they will be referred to the community health service centers to receive the follow-up intervention over 6 months provided by general practitioners (GPs) and community nurses (second stage of intervention). Health professionals from both hospital and community health service centers will be resourced to work in a collaborative way to implement the postdischarge interventions. A flow chart of the intervention protocol is shown in Fig. 4 and discussed in the following.

**Fig. 4 Fig4:**
[figure not shown]
Flow chart of the intervention protocol. BP blood pressure, CHSC community health service center, GP general practitioner

#### Stage 1: interventions at hospital

1.1.Individualized discharge education.Patients will be given two face-to-face individualized health education sessions specific to diabetic patients with hypertension by the in-charge nurse. The health education includes health behavior education, disease-associated education and medication education with 15 min for each session. A geriatrics condition screening will also be undertaken using the widely recognized evidence-based screening tool “Fulmer SPICES Comprehensive Assessment Tool for Older Adults” [31]. Education on preventing and managing geriatric conditions will be provided by the in-charge nurse based on the findings from the screening.1.2.Lifestyle modification goals: intervention diary—patient version.1.2.1.Patients will be asked to establish lifestyle modification goals and develop personal action plans with the in-charge nurse. Patients will be provided an “intervention diary—patient version” (Additional file 2) to document their lifestyle modification goals, personal action plans, progress toward the goals, medication adherence, adverse events and unplanned hospital admissions/use of emergency care services.1.2.2.Patients will be asked to discuss and establish their diet plan with the in-charge nurse. The diet plan will be recorded in the “intervention diary—patient version”.1.3.Individualized medication treatment.Prior to discharge, patients will be given an individualized medication treatment plan by the medical specialist. Individualized medication treatment will be recorded in the “intervention diary—patient version”.1.4.Referral to the community health service center: intervention record—community nurse and GP version.1.4.1.When patients are discharged from hospital, they will be referred to a community health service center by the in-charge nurse for regular follow-up over 6 months. An “Intervention record—community nurse and GP version” (Additional file 3) will be sent to the community nurse by the in-charge nurse on discharge to record the required postdischarge interventions and outcomes.1.4.2.In order to establish collaboration and maintain communication among the doctor and nurse at the hospital, the patient and the GP and nurse at the community health service center, a two-way referral letter has been developed (Additional file 4).1.4.3.The in-charge nurse at the hospital will contact the GP and nurse in the community health service center through a telephone call and will fill in the two-way referral letter for patients.1.4.4.The in-charge nurse will help patients to contact the nearby community health service center for the follow-up visit. Patients will be advised of the community health service center they have been referred to, and the name and contacts of the GP and nurse in the community health service center.1.4.5.Data in relation to the patient’s demographic information, pharmacotherapy history and other clinical information will be sent to the community nurse by the in-charge nurse on discharge.1.4.6.Patients will take the referral letter and discharge abstract to the community health service center for the follow-up visit.1.5.Monitoring.The in-charge nurse at the hospital will keep track of the patient’s referral progress through making telephone calls with the patients and community nurses to ensure patients are seen at the community health service center.

#### Stage 2: regular follow-up interventions over 6 months at community health service centers

2.1.Fortnightly telephone call.Patients will receive a fortnightly telephone call at home from the community nurse to monitor their progress toward setting goals and medication adherence.2.2.Monthly community health service center visit.Patients will be asked to visit the community nurse and GP at the community health service center every month for follow-up visits.2.2.1.Patients will receive blood pressure measurement every month by the community nurse.2.2.2.Patients will receive a review and assessment from the community nurse on their adherence to medication and lifestyle recommendations, and their progress toward lifestyle modification goals.2.2.3.Patients will receive reinforced health education from the community nurse to improve their self-management ability and treatment adherence. Patient will be given health education on preventing or treating geriatric conditions based on the “Fulmer SPICES Comprehensive Assessment Tool for Older Adults”.2.2.4.Patients will receive an assessment from the GP on their clinical outcomes, problems of nonadherence to medication, medication side effects, drug therapy problems, drug-related needs and clinical events occurred.2.2.5.Patients will be asked to discuss their individualized treatment plan and medication adjustment with the GP.2.2.6.Patients will be asked to document their medication changes in the “intervention diary—patient version”.2.2.7.Patients will be reminded of the categories, dosage and frequency of medication required to be taken prior to the next visit by community nurse.2.3.GP and medical specialist collaboration.The GP will discuss with the medical specialist at the hospital via email or telephone when necessary to adjust medication. BP, HbA1c and lipid readings will be recorded by the community nurses and formatted as a monthly report and then sent to medical specialists for review. Urgent symptoms will be communicated to the medical specialist immediately for additional orders by the GP.

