### Usual care

In the usual care group, patients will receive routine discharge education at hospital. After they are discharged, they will go to their usual outpatient clinic of the hospital to receive follow-up and outcome measures at 3 and 6 months. They will not be referred to the community health service center. They will be asked to record the number of adverse events and unplanned hospital admissions/use of emergency care services during 3-month and 6-month follow-up in a usual care table (Additional file 5). The researcher will record the HbA1c and lipid levels close to the 3-month and 6-month follow-up from the patients’ medical record.

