### Outcome measures

#### Primary outcome

The primary outcome is systolic blood pressure at 6-month follow-up adjusted for baseline value. At each measurement point, blood pressure will be measured three times at 5-min intervals on the participant’s right arm in a sitting position. The average of the three blood pressure readings will be calculated as the final BP reading for each group at each time point, which minimizes measurement error.

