### Data collection

At baseline, the in-charge nurse will distribute the questionnaires to participants or their family caregiver. They will complete the questionnaires once the consent form is signed and before the individualized discharge education is provided. The patient’s in-charge nurses at the hospital will provide assistance to participants should they have any questions about the questionnaire. Clinical outcomes (BP, HbA1c and lipid values) will be directly recorded from the health record of patients by a research assistant.

At 3-month and 6-month follow-up, community nurses will distribute the questionnaires to participants in the intervention group when they visit the community health service center. Community nurses will be available to assist patients should they have any questions about the questionnaire. In the usual care group, a nurse in the medical specialist clinics will distribute the questionnaire to participants when they visit the outpatient clinic at 3-month and 6-month follow-up. The nurse will be available to assist patients should they have any questions.

Completed questionnaires will be placed in a prepared sealable envelope to maintain confidentiality. The researcher will prepare a drop box in each ward, community health service center and outpatient clinic. Participants will return the sealed questionnaires to the drop box. The research assistants will collect completed questionnaires on a weekly basis.

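### As described, the 3- and 6-month systolic blood pressure appears to be taken in a different setting and by a different kind of assessor in each arm, so any systematic measurement difference enters the treatment effect

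*Protocol article*

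**What the plan says.** All references are to the protocol article.

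- **Endpoint** (Primary outcome): "The primary outcome is systolic blood pressure at 6-month follow-up adjusted for baseline value". The technique is common to both arms: "At each measurement point, blood pressure will be measured three times at 5-min intervals on the participant’s right arm in a sitting position". The section names no assessor, place or device.
- **Intervention arm** (Stage 2, items 2.2.1 and 2.3): "Patients will receive blood pressure measurement every month by the community nurse", and "BP, HbA1c and lipid readings will be recorded by the community nurses and formatted as a monthly report". Stage 1, item 1.4.1 sends the community nurse a record form that covers outcomes as well as interventions. The same nurse makes the fortnightly calls, reviews adherence and gives the reinforcing education.
- **Usual-care arm** (Usual care): "they will go to their usual outpatient clinic of the hospital to receive follow-up and outcome measures at 3 and 6 months". These patients are not referred to a community center.
- **Hospital follow-up in the intervention arm** (Description of the interventions): "in addition to the usual follow-up in the hospital outpatient clinic, they will be referred to the community health service centers".
- **Blinding** (Blinding and allocation concealment): staff who deliver the intervention know the allocation. Blinding covers the recruiter, the participants until baseline is complete, and the statistician. No blinded blood pressure assessor is named.
- **Baseline** (Data collection): "Clinical outcomes (BP, HbA1c and lipid values) will be directly recorded from the health record of patients by a research assistant".

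**The concern.** Blood pressure readings depend on who takes them, where, and with which device. If the intervention arm is read at a community center by an unblinded nurse who is treating the patient, and the usual-care arm is read at a hospital clinic, then any systematic difference between those two arrangements is indistinguishable from a treatment effect on the primary outcome. The limitations listed in the Discussion recognise reporting bias for the self-completed questionnaires only, so this risk to the primary comparison is not acknowledged.

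A second, separate matter is the baseline value. The Primary outcome section requires the three-reading procedure at every measurement point, while Data collection takes baseline blood pressure from the health record without saying that the recorded value was obtained by that procedure.

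**Working it through.** **1. Is follow-up setting separable from arm?** Setting the sections side by side:

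| | Intervention | Usual care |
|---|---|---|
| Baseline blood pressure | Health record | Health record |
| 3- and 6-month place | Community center (inferred) | Hospital outpatient clinic (stated) |
| Assessor | Treating community nurse (inferred) | Not named |
| Assessor aware of allocation | Yes | Not stated |

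The source of the baseline is the same in both arms, and the follow-up setting then splits completely by arm. Statistical methods specifies random intercepts for ward and for participant within ward, a group by time interaction, and adjustment for baseline and listed covariates. None of these contains information that separates a follow-up setting or assessor shift from treatment, and the group by time term would absorb it. Averaging three readings reduces random error but not a systematic shift.

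**2. The plan's own power figure.** Inputs from Sample size: difference 7.3 mmHg, SD 12.1 mmHg, 5 clusters per arm, 25 completers per cluster (125 per arm), ICC 0.05, power 80%. Statistical methods gives a significance level of 0.05; two-sided is assumed.

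- Design effect = 1 + (25 − 1) × 0.05 = 2.20. The stated 1.48 is √2.20, the inflation of the standard error.
- SE of the arm difference = 12.1 × √(2 × 2.20 / 125) = 2.27 mmHg.
- Degrees of freedom = 2 × 5 − 2 = 8; critical t = 2.306.
- Non-centrality = 7.3 / 2.27 = 3.22, giving power of 80.4%.

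The stated 80% is reproduced, so 2.27 mmHg on 8 degrees of freedom is a fair working precision.

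**3. Consequence of a measurement shift b.** The documents give no value for b; 1 to 5 mmHg is an assumption.

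- False-positive rate with no true effect: P(|t₈| > 2.306) with non-centrality b / 2.27.
- Power if the shift works against the intervention and the true effect is 7.3 mmHg: non-centrality (7.3 − b) / 2.27.

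| Assumed shift b (mmHg) | Share of 7.3 | False-positive rate, shift favours intervention | Power, shift opposes intervention |
|---|---|---|---|
| 0 | 0% | 5.0% | 80.4% |
| 1 | 14% | 6.8% | 68.2% |
| 2 | 27% | 12.2% | 53.7% |
| 3 | 41% | 21.5% | 38.5% |
| 4 | 55% | 34.2% | 24.9% |
| 5 | 68% | 49.1% | 14.4% |

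**4. Baseline.** Chart extraction applies to both arms, so it does not contribute to the confounding in step 1. The open question is whether the chart value follows the three-reading rule. If it does not, the covariate in the primary comparison is measured differently from the follow-up value.

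**The case against.** The strongest reply is that the protocol never says that the community nurse's reading is the endpoint. Item 2.2.1 describes monthly monitoring as part of the intervention. The endpoint is defined elsewhere, with one technique for both arms, and intervention patients keep their hospital outpatient follow-up, so a common setting is possible. The SPIRIT figure, the intervention flow chart and the community nurse's record form are not visible here and may settle the matter. This stands as a limit on certainty. It does not remove the point: no other post-discharge reading is described for that arm, the record form covers outcomes, and Data collection places the 3- and 6-month questionnaires at the community center for one arm and at the specialist clinic for the other.

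A reader might also infer that the shift must favour the intervention, because the nurse is treating the patient and the center is local. The documents do not support this. They say nothing about how readings differ by setting, they call the hospital clinic the patients' usual one, and the Background reports low consideration of community centers in another Chinese city. Relative familiarity is therefore not established, and both directions have to be considered.

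Third, the common technique limits procedural differences. That is true, but it leaves assessor, place, device and knowledge of allocation uncontrolled.

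Finally, a reader might count the chart baseline as part of the confounding. It is not, since both arms share it. Nor is it a certain contradiction: ward staff could take three readings and enter them in the record for later extraction. The text needs to say so.

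**Conclusion.** The point holds in this form: on the most natural reading, measurement setting and assessor are aligned with arm for the primary outcome, the intervention-arm assessor is an unblinded treater, and no planned analysis can separate a resulting shift from treatment. This rests on the inference that the community-center reading supplies the intervention arm's endpoint.

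Size and direction are unknown. The figures are conditional on an assumed shift of 1 to 5 mmHg and the planned SE of 2.27 mmHg on 8 degrees of freedom: a false-positive rate of about 7% to 49% if the shift favours the intervention, or, for a 3 mmHg shift the other way, power of about 38% in place of 80%. They show how sensitive the trial would be to such a shift; they are not evidence that one exists. The baseline matter is a separate and smaller inconsistency between two sections.

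**What to change.** For visits still to come:

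- Define the primary 3- and 6-month systolic pressure in both arms as the three-reading mean taken at the hospital outpatient visit, which both arms are described as attending. Use the same device model and existing clinic staff who do not deliver the intervention.
- Use community-center readings for care only, not as endpoint values.
- Record site and assessor for every reading, and run a sensitivity analysis covering endpoint readings already taken at community centers.
- Separately, reconcile Primary outcome with Data collection, so that the baseline taken from the record is a three-reading value obtained before allocation is disclosed.

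**Cost.** This is a protocol clarification using existing staff and visits, but it is not free. The protocol gives no timing for intervention patients' outpatient visits, which would have to fall near months 3 and 6. Attendance at the hospital may differ by arm, because the programme moves care towards the community, so missing endpoint data should be monitored by arm. The trial began in June 2017 and was still recruiting at submission, so early participants will have mixed measurement sites and chart baselines. Aligning the setting also does not guarantee blinding: clinic staff who do not deliver the intervention may still learn the allocation.
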